### 13.1.2 BI-participants

Data from our previous high-dose naloxone study (Pereira MP et al [2015] PLOS One 10: e0134441. 10.1371/journal.pone.0134441 [doi]) indicate:

1. for the high-sensitizers ( $n = 3$ ): secondary hyperalgesia areas 168 hrs after the BI during placebo infusion, mean (SD),  $2.1 \text{ cm}^2$  ( $2.5 \text{ cm}^2$ ) and during naloxone infusion  $111.0 \text{ cm}^2$  ( $26.3 \text{ cm}^2$ ).
2. for the low-sensitizers ( $n = 3$ ): secondary hyperalgesia areas 168 hrs after the BI during placebo infusion,  $0.3 \text{ cm}^2$  ( $0.1 \text{ cm}^2$ ) and during naloxone infusion  $0.9 \text{ cm}^2$  ( $0.6 \text{ cm}^2$ ).

Using the significance level  $\alpha$  set to 0.01 and the power set to  $= 0.90$  ( $\beta = 0.10$ ), the estimated number of individuals needed to reject the null hypothesis in the high-sensitizers are 5 (effect size 4.1; sic!) and in the low-sensitizers are 18 (effect size 1.4). Since the data used for sample size estimates are made on an extremely limited number of individuals, and, since the study of nature is a proof-of-concept, it was decided to include 20 high-sensitizers and 20 low-sensitizers. Boot-strapping techniques could have been used, but we considered the number individuals used in the sample estimate too extreme. On the other hand, if a larger number of subjects are needed, the clinical significance is deemed of dubious value.

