We therefore initiated another translational study in which we hypothesized that a higher dose of naloxone (2 mg/kg) would reinstate secondary hyperalgesia in human patients following resolution of a mild burn-injury and thus show latent sensitization in humans. We demonstrated in 4 out of 12 patients, that naloxone administered 7 days after a mild burn injury was associated with reinstatement of secondary hyperalgesia [12]. This study thus raises two important questions: *first*, is it possible to foresee individuals who will demonstrate latent sensitization upon challenge with an injury, and, *second*, will challenge with a larger tissue injury, including more extensive inflammatory reactions, induce a higher relative number of responders.

Consequently, our aim in the present study, is twofold. *First*, to investigate if naloxone will reinstate clinical pain and hyperalgesia after resolution of a more pronounced inflammatory injury in a postsurgical model, i.e., three to four weeks after a unilateral, impacted mandibular third molar extraction procedure. At this time point, patients are expected to be pain free at rest and only have mild pain during specific movements. We expect in this way to contribute with further knowledge on the role of the endogenous opioid-system in latent sensitization, following a mild thermal injury and clinically relevant surgery-related tissue injury. *Second*, in volunteers, to investigate if high-sensitizers (*a priori* developing large areas of secondary hyperalgesia after exposure to a mild burn-injury) are more prone

to demonstrate latent sensitization following naloxone administration, than low-sensitizers (*a priori* developing small areas of secondary hyperalgesia).

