## 2. AIM

The principal aims of the study are:

\* *first*, to investigate whether the administration of naloxone, a selective mu-opioid receptor (MOR) antagonist, can re-introduce clinical pain (at rest, during movement and in pressure-evoked condition) and hyperalgesia three to four weeks after a unilateral, mandibular third molar extraction procedure (TME).

\* *second*, to assess predictability of the latent sensitization response, assessed as naloxone-induced reinstatement of secondary hyperalgesia after resolution of an experimental burn-injury, according to individual sensitization phenotype (high-sensitizers vs. low-sensitizers).

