## 6.2 BI-participants

|                |                                                         |
|----------------|---------------------------------------------------------|
| Study type:    | Randomized, placebo-controlled, double-blind crossover  |
| Randomization: | Computer generated randomization list, closed envelopes |
| Phase:         | Phase 2                                                 |
| Blinding:      | Double-blind, crossover                                 |
| Subjects:      | Healthy volunteers                                      |
| Number:        | Day 0: 80 subjects; Day 1-4: 40 evaluable subjects      |

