### 13.2.1 BI-participants

To test if data is normally distributed, residual plots and the Kolmogorov-Smirnov test will be used (SPSS 20.0, Chicago, IL, USA; MedCalc Software: version 12.07.0.0; Mariakerke, Belgium). In case of non-normal data distribution, primarily a logarithmic transformation is tried or secondarily a Box-Cox transformation will be attempted for normalization of data.

The differences calculated are:

$$\Delta\text{SHA}_{\text{high-sensitizers}} = \text{SHA}_{\text{NX high-sensitizers}} - \text{SHA}_{\text{PL high-sensitizers}} \text{ (max. values during one of the 3 TCI-steps)}$$

$$\Delta\text{SHA}_{\text{low-sensitizers}} = \text{SHA}_{\text{NX low-sensitizers}} - \text{SHA}_{\text{PL low-sensitizers}} \text{ (max. values during one of the 3 TCI-steps)}$$

$$\Delta\text{SHA}_{\text{sensitizers}} = \Delta\text{SHA}_{\text{high-sensitizers}} - \Delta\text{SHA}_{\text{low-sensitizers}}$$

A mixed model with random effect for subject and fixed-effects for the factors: *secondary hyperalgesia areas* (SHA); *sensitizers* (high-sensitizers/low-sensitizers); *target-controlled-infusion* (step 1/step 2/step 3); *HADS-scores*; and *PCS-scores*, are used for the primary outcome  $\Delta\text{SHA}_{\text{sensitizers}}$ . Non-significant ( $P > 0.05$ ) factors, beginning with interactions, are excluded until all included factors attain significance. Main-effects and interaction-effects are examined.

The risk of type I error is reduced by setting a significance level of 0.01 ( $\alpha$ ). A power of 0.90 ( $\beta = 0.10$ ) is set in order to reduce the risk of type II errors. For all statistical calculations, in which multiple comparisons are performed, Duncan's new multiple range test or Scheffé's method, as appropriate, will be used. Statistical calculations will be performed with partially un-blinded data, i.e., group A and B. When statistics have been completed data are unblinded into naloxone and placebo groups.

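### Section 13.1.2 sizes the two burn-injury strata of one crossover with different formulas, so 18 at effect size 1.4 is not a crossover result, and no calculation is given for the primary high-minus-low contrast

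*Protocol*

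**What the plan says.** The burn-injury (BI) study is described in section 6.2 as "Randomized, placebo-controlled, double-blind crossover", so each participant receives both naloxone and placebo.

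Section 13.1.2 takes pilot means and SDs of the secondary hyperalgesia area at 168 hours, from 3 subjects per stratum:

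- High-sensitizers: placebo 2.1 (SD 2.5) cm², naloxone 111.0 (SD 26.3) cm².
- Low-sensitizers: placebo 0.3 (SD 0.1) cm², naloxone 0.9 (SD 0.6) cm².

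With alpha "set to 0.01 and the power set to" 0.90, it reports 5 high-sensitizers (effect size 4.1), "and in the low-sensitizers are 18 (effect size 1.4"). It then calls the pilot data extremely limited, describes the study as proof-of-concept, and sets 20 per stratum.

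The second aim (section 2) is to predict the naloxone response "according to individual sensitization phenotype (high-sensitizers vs. low-sensitizers"). Section 13.2.1 (BI-participants) names ΔSHA(sensitizers) as the primary outcome: the naloxone-minus-placebo difference in high-sensitizers minus the same difference in low-sensitizers. That section repeats alpha 0.01 and "A power of 0.90". No within-subject correlation is given for the BI study.

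**The concern.** Two things look wrong. First, both strata follow the same crossover and should be sized by the same kind of calculation, yet the two reported pairs do not come from one formula. Second, both calculations ask whether naloxone differs from placebo inside a stratum. The primary outcome asks whether that difference itself differs between strata, and nothing in section 13.1.2 addresses this.

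At stake is whether the stated alpha and power have any basis for the primary contrast, and whether 20 low-sensitizers are enough once the formula is corrected.

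**Working it through.** **Method.** Exact noncentral-t power, alpha 0.01, power 0.90. The protocol does not state sidedness. Two-sided is assumed because it reproduces both printed numbers, while one-sided gives 15 and 4.

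**1. Reproducing the printed figures**

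High-sensitizers, paired, r = 0:
- Mean difference = 111.0 − 2.1 = 108.9
- SD of differences = √(2.5² + 26.3²) = 26.4
- Effect size = 108.9 / 26.4 = 4.12, n = 5. This matches. The unpaired version would be 108.9 / 18.68 = 5.83, with 3 per group.

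Low-sensitizers, unpaired:
- Mean difference = 0.9 − 0.3 = 0.6
- Pooled SD = √((0.1² + 0.6²)/2) = 0.430
- d = 0.6 / 0.430 = 1.395, n = 18 per group (power 89.9% at 17, 92.0% at 18). This matches.

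Each pair reproduces, but only if a different design is used for each stratum.

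**2. Low-sensitizers as a crossover**

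SD of differences = √(0.1² + 0.6² − 2r × 0.1 × 0.6) = √(0.37 − 0.12r), and dz = 0.6 / SD of differences.

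| r | SD of differences | dz | n for 90% | power at 20 |
|---|---|---|---|---|
| −1 | 0.700 | 0.86 | 24 | 82% |
| −0.5 | 0.656 | 0.91 | 22 | 87.5% |
| −0.25 | 0.632 | 0.95 | 20 | 90.1% |
| 0 | 0.608 | 0.99 | 19 | 92.5% |
| 0.25 | 0.583 | 1.03 | 18 | 94.7% |
| 0.5 | 0.557 | 1.08 | 17 | 96.5% |
| 1 | 0.500 | 1.20 | 14 | 98.9% |

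A paired effect size of 1.4 needs 12 subjects (power 89.8% at 11, 93.4% at 12), so 1.4 and 18 cannot belong to the same paired calculation.

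**3. The primary contrast, for which the protocol gives no calculation**

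- Pilot contrast = 108.9 − 0.6 = 108.3 cm²
- SDs of the per-subject differences at r = 0: 26.4 and 0.61. Pooled = √((26.4² + 0.61²)/2) = 18.7
- d = 108.3 / 18.7 = 5.8 (5.3 to 6.4 over r from −1 to 1)
- Required: 3 to 4 per group with pooled variance, about 5 with Welch. Power at 20 + 20 is near 100%.
- Detectable with 90% power at 20 + 20: d = 1.28, or 1.28 × 18.7 ≈ 24 cm²

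**4. Stress case (my assumptions)**

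The pilot means imply that every high-sensitizer responds. Suppose instead that a fraction p respond as in the pilot, the rest show no change, and no low-sensitizer responds. The mean difference is then 108.9p, the variance in high-sensitizers is 26.4²p + 108.9²p(1 − p), and d = mean / √(variance/2).

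- p = 1/2: mean 54.5, SD 57.6, d = 1.34, power about 93%
- p = 1/3: mean 36.3, SD 53.6, d = 0.96, power about 63%

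These are normal-theory values. Simulating the two-point mixture gives about 97% and 66% with the pooled t-test, and about 94% and 52% with Welch.

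**The case against.** The strongest reply is that the trial's sample size is 20 + 20, not 18. Section 13.1.2 rests that choice on the proof-of-concept aim and openly admits how thin the pilot is. The corrected low-sensitizer requirement at r between 0 and 0.5 is 17 to 19, which brackets the printed 18, and the primary contrast is amply powered on the pilot figures. This stands, and it limits the point to a correction of stated figures.

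Three stronger readings are tempting, and the protocol supports none of them:

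- **That 1.4 is impossible from the stated SDs.** It is exactly the unpaired d from those SDs. It is out of reach only as a paired effect size with the SDs as printed. Even that limit treats one-decimal inputs as exact: at the rounding extremes (difference 0.7, SDs 0.15 and 0.55), a paired 1.4 is reached at r of about 0.5. The 18 would still not follow, because a paired 1.4 needs 12.
- **That the planned number is too small.** Twenty low-sensitizers fall below 90% power only for correlations more negative than about −0.25, and nothing in the protocol points there.
- **That real power for the primary contrast is 63%.** The one-third figure borrows the overall pilot rate ("We demonstrated in 4 out of 12 patients", section 1.1) and applies it to subjects selected as high-sensitizers, which assumes no enrichment. The pilot high-sensitizers suggest otherwise: with n = 3, mean 111.0 and SD 26.3, every value must exceed 80 cm². On the other side, 3 of 3 has an exact 95% interval of 29% to 100%, so the case is a fair stress test but not an estimate.

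It can also be said that section 13.2.1 does attach alpha 0.01 and power 0.90 to the primary contrast. It does. What is missing is the calculation behind them.

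**Conclusion.** The point holds as a correction of stated figures. Section 13.1.2 mixes a paired and an unpaired formula for one crossover, and the low-sensitizer pair is not a valid crossover result. On the formula used for the high-sensitizers it would be 0.99 with n = 19. The primary high-minus-low contrast carries a stated power of 0.90 with no calculation behind it.

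The consequence for the trial is small. On the protocol's own inputs, 20 per stratum remains adequate in low-sensitizers for r of about −0.25 and above, and gives power near 100% for the primary contrast. This rests on two-sided testing, the SDs as printed, an unstated within-subject correlation, and a pilot of 3 subjects per stratum. The last is the weakest support: the margin on the primary contrast depends on most high-sensitizers responding as those three did.

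**What to change.** In section 13.1.2:

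1. Use one paired method for both strata and state the assumed correlation and sidedness. At r = 0 the low-sensitizer line becomes effect size 0.99, n = 19, with 92.5% power at 20. Alternatively, delete the low-sensitizer figure.
2. Add a two-sample calculation for the per-subject naloxone-minus-placebo difference, high versus low, at alpha 0.01. State that 20 + 20 detects d = 1.28 with 90% power (about 24 cm² with the pilot SDs), against a pilot contrast of about 108 cm² (d about 5.8).
3. Optionally, show power for responder fractions in high-sensitizers from one third to one, labelled as a stress case because the pilot has 3 subjects per stratum.

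The cost is restated figures and a few added lines. The 20 + 20 and the study procedures do not change.

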## 13.2 Data processing

### 13.2.1 TME-participants

To test if data is normally distributed, residual plots and the Kolmogorov-Smirnov test will be used (SPSS 20.0, Chicago, IL, USA; MedCalc Software: version 12.07.0.0; Mariakerke, Belgium). In case of non-normal data distribution, primarily a logarithmic transformation is tried or secondarily a Box-Cox transformation will be attempted for normalization of data.

The primary outcome  $\Delta\text{SPID}$  ( $\text{SPID}_{\text{NX}} - \text{SPID}_{\text{PL}}$ ) is analyzed by one-way repeated measures ANOVA ( $\Delta\text{SPID}$ : dependent variable; TCI-steps: independent variable) or a corresponding non-parametric analogue (Friedman test), as appropriate. Paired  $t$ -test or Wilcoxon rank sum test will be used, as appropriate for inter-group comparisons.

A mixed model with random effect for subject and fixed-effects for the factors; *target-controlled-infusion* (step 1/step 2/step 3), *drug* (naloxone/placebo); *secondary hyperalgesia area* (SHA); *pressure pain threshold* (PPT); *HADS-score*; and *PCS-scores*, are used for the primary outcome  $\Delta\text{SPID}$  ( $\text{SPID}_{\text{NX}} - \text{SPID}_{\text{PL}}$ ). Non-significant ( $P > 0.05$ ) factors, beginning with interactions, are excluded until all included factors attain significance. Main-effects and interaction-effects are examined.

The risk of type I error is reduced by setting a significance level of 0.01 ( $\alpha$ ). A power of 0.90 ( $\beta = 0.10$ ) is set in order to reduce the risk of type II errors. For all statistical calculations, in which multiple comparisons are performed, Duncan's new multiple range test or Scheffé's method, as appropriate, will be used. Statistical calculations will be performed with partially un-blinded data, i.e., group A and B. When statistics have been completed, data are unblinded, into naloxone and placebo groups.

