### 13. STATISTICAL ANALYSES

#### 13.1 Sample size calculations

##### 13.1.1 TME-participants

Sample size calculations are based on following assumptions and estimations (abbreviations: BL = baseline; NX = naloxone; PL = placebo; TCI = during target-controlled-infusion):

1. a primary outcome based on a summed measure (SM) of resting pain (RP), masticatory pain (MP; (movement-related) and pressure-evoked pain (PM; pressure algometry [100 kPa]).  $NRS_{SM} = NRS_{RP} + NRS_{MP} + NRS_{PM}$ .
2. the summed pain intensities (SPIs) are calculated as: (BL-SPINX) and (TCI-SPINX), and, (BL-SPIPL) and (TCI-SPIPL), where (TCI-SPI) indicates SM-value at highest obtainable TCI-step (Fig. 2).
3. the summed pain intensity differences (SPIDs) are the differences: **SPIDNX** = (TCI-SPINX) – (BL-SPINX) and **SPIDPL** = (TCI-SPIPL) - (BL-SPIPL)

4. the mean [SD] BL-pain intensities are estimated to be: resting pain 1 [1] NRS-units; movement related pain 2 [2] NRS-units; pressure evoked pain 4 [2] NRS-units.
5. the mean [SD] summed BL-pain intensity (BL-SPI) is estimated to be 7 [4.1] NRS-units (Table 2).
6. the minimal relevant SPID-difference, calculated as  $\Delta SPID = SPID_{NX} - SPID_{PL}$  is estimated to be 5 (NX-group: RP = 4; MP = 5; PM = 7 [total 16]/PL-group: RP = 2; MP = 4; PM = 5 [total 11]) corresponding to a  $\Delta SPID\% = 45\%$ .
7. the design is a placebo-controlled, randomized, double-blind, crossover study
8. the significance level  $\alpha$  is set to 0.01 and the power is set to  $= 0.90$  ( $\beta = 0.10$ )

The total number of individuals estimated to be included in the study is calculatedE to be 14 (effect size 1.2). Using the range of variances in Table 2, it can be calculated that the number of individuals ranges from 9 to 19, with effect sizes of 1.7 to 1.0, respectively.

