In order to allow for drop-outs the total number of individuals is set to 18. Due to the frail nature of the sample size estimates, an interim-analysis of the primary outcome, performed by an independent statistician, is made after per-protocol inclusion of 14 individuals. If the null hypothesis (no statistical difference between the placebo and the naloxone groups) is rejected, the study is deemed completed. If the new sample size estimates indicate that more than 16 additional individuals (total number of individuals > 30) are required, the study is prematurely discontinued. If less than 16 additional individuals (total number of individuals  $\leq 30$ ) the study continues and is discontinued after the stipulated number has been reached.

| V(X1) | V(X2) | V(X3) | COV(X1,X2) | COV(X1,X3) | COV(X2,X3) | V(SUM) | SD(SUM) | CORR(X1,X2) | CORR(X1,X3) | CORR(X2,X3) |
|-------|-------|-------|------------|------------|------------|--------|---------|-------------|-------------|-------------|
| 1     | 4     | 4     | 0          | 0          | 0          | 9      | 3.00    | 0           | 0           | 0           |
| 1     | 4     | 4     | 0.1        | 0.1        | 0.2        | 9.8    | 3.13    | 0.05        | 0.05        | 0.05        |
| 1     | 4     | 4     | 0.2        | 0.2        | 0.4        | 10.6   | 3.26    | 0.1         | 0.1         | 0.1         |
| 1     | 4     | 4     | 0.3        | 0.3        | 0.6        | 11.4   | 3.38    | 0.15        | 0.15        | 0.15        |
| 1     | 4     | 4     | 0.4        | 0.4        | 0.8        | 12.2   | 3.49    | 0.2         | 0.2         | 0.2         |
| 1     | 4     | 4     | 0.5        | 0.5        | 1          | 13     | 3.61    | 0.25        | 0.25        | 0.25        |
| 1     | 4     | 4     | 0.6        | 0.6        | 1.2        | 13.8   | 3.71    | 0.3         | 0.3         | 0.3         |
| 1     | 4     | 4     | 0.7        | 0.7        | 1.4        | 14.6   | 3.82    | 0.35        | 0.35        | 0.35        |
| 1     | 4     | 4     | 0.8        | 0.8        | 1.6        | 15.4   | 3.92    | 0.4         | 0.4         | 0.4         |
| 1     | 4     | 4     | 0.9        | 0.9        | 1.8        | 16.2   | 4.02    | 0.45        | 0.45        | 0.45        |
| 1     | 4     | 4     | 1          | 1          | 2          | 17     | 4.12    | 0.5         | 0.5         | 0.5         |

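### The test assigned to the TME primary outcome asks whether the naloxone–placebo difference changes between infusion steps, not whether it is zero

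*Protocol*

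**What the plan says.** Protocol section 13.1.1 sums three NRS ratings (rest, mastication, pressure at 100 kPa). It takes one during-infusion value per session, the "value at highest obtainable TCI-step (Fig. 2", subtracts baseline to give SPID, and sets ΔSPID = SPID on naloxone minus SPID on placebo. The planning difference is 5 NRS-units, the SD 4.1, α 0.01 and power 0.90, giving 14 subjects, or 9 to 19 over the variances in Table 2. The interim rule in the same section states the null hypothesis as "no statistical difference between the placebo and the naloxone groups" and ends the study if it is rejected.

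Section 13.2.1 then says that ΔSPID "is analyzed by one-way repeated measures ANOVA", with the roles given as "dependent variable; TCI-steps: independent variable) or a corresponding non-parametric analogue (Friedman test), as appropriate". The next sentence adds that a paired t-test or "Wilcoxon rank sum test will be used, as appropriate for inter-group comparisons". A further paragraph describes "A mixed model with random effect for subject and fixed-effects for the factors" TCI-step, drug (naloxone/placebo), secondary hyperalgesia area (SHA), pressure pain threshold (PPT), HADS and PCS. Its outcome is again ΔSPID, and non-significant "factors, beginning with interactions, are excluded until all included factors attain significance".

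**The concern.** Once naloxone and placebo have been subtracted, the drug effect is the mean of ΔSPID. An ANOVA or Friedman test across steps removes that mean and looks only at differences between steps, so it is in effect a drug-by-step test. A drug effect of the same size at all three steps is invisible to it.

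The mixed model does not repair this, because a ΔSPID record belongs to neither drug and the drug factor has nothing to estimate. The one sentence that does name a drug comparison leaves open the outcome, the step and whether it is primary, and its non-parametric option is a test for independent samples. At stake are the confirmatory result of the TME study and the interim decision: both need a test of the stated null, and the plan does not say which test decides.

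**Working it through.** **1. Reproduce the sample size.** Inputs from section 13.1.1: difference 5, α = 0.01, power 0.90. Table 2 gives V(SUM) = 17 at correlation 0.5, so SD = √17 = 4.12; its extremes are SD 3.00 and 5.00. For a paired t-test on ΔSPID, d = 5/SD, with power from the noncentral t distribution (n − 1 df, noncentrality d√n), two-sided.

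| SD | d | Smallest n | Power at that n | Protocol |
|---|---|---|---|---|
| 3.00 | 1.67 | 9 | 0.91 | 9 |
| 4.12 | 1.21 | 14 | 0.91 | 14 |
| 5.00 | 1.00 | 19 | 0.91 | 19 |

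All three figures match. One-sided testing gives 12 (range 8 to 16) and the normal approximation 11. The trial was therefore sized for a two-sided paired test of mean ΔSPID = 0.

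**2. Compare the nulls.** Write δ1, δ2, δ3 for the mean ΔSPID at the three steps.
- Interim rule and sample size: H0 is δ = 0, at the highest step.
- ANOVA or Friedman test on TCI-step: H0 is δ1 = δ2 = δ3, whatever their common value.

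Under the definition in 13.1.1 there is also only one ΔSPID per subject, which leaves no step factor to analyse.

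**3. Size of the mismatch.** Simulation with n = 14, SD 4.12 at each step and α = 0.01. The between-step correlation is not in the protocol; 0.3 to 0.8 is assumed. The dose-proportional row scales 5 by the estimated plasma concentrations in section 11.1: 5 × 344/3,196 = 0.54 and 5 × 1,059/3,196 = 1.66.

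| True ΔSPID at steps 1/2/3 | Step ANOVA rejects | Paired t-test, last step |
|---|---|---|
| 5 / 5 / 5 | about 1% | 91–92% |
| 3 / 4 / 5 | 8–41% | 91–92% |
| 1.67 / 3.33 / 5 | 30–93% | 91–92% |
| 0.54 / 1.66 / 5 | 65–99.9% | 91–92% |
| 0 / 0 / 5 | 88–100% | 91–92% |

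The low end of each range is correlation 0.3 and the high end 0.8. The Friedman test with 5 at every step rejects in about 0.5% of runs (correlation 0.5).

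**4. The mixed model.** With ΔSPID as outcome there is one record per subject and step. Columns for intercept, two step contrasts and a constant drug column have rank 3 of 4. Copying each ΔSPID to both drug levels instead gives a drug coefficient of exactly 0. Neither yields a drug effect.

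**5. Rank sum against signed rank.** n = 14, difference 5, SD of the within-subject difference held at 4.12, so each session's SPID has SD 4.12/√(2(1 − ρ)). The within-subject correlation ρ is assumed.

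| ρ | Rank sum | Signed rank |
|---|---|---|
| 0 | about 93% | about 89% |
| 0.3 | 82% | 89% |
| 0.5 | 63% | 88% |
| 0.7 | 31% | 88% |

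**The case against.** The strongest reply is that the protocol does contain a drug comparison. The sentence after the ANOVA names a paired t-test for comparisons between groups, the protocol uses that word for naloxone and placebo, and the sample size is exactly that of such a test. This stands. A reader might infer that the plan never compares naloxone with placebo, and the text does not support that. What is missing is the designation of that test as primary, on ΔSPID, at a stated step.

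Second, the dose triples at each step, so a flat effect is the extreme case. This also stands: with a steep rise and correlated steps the ANOVA rejects as often as the paired test or more often. The contrast of 1% with 92% is not the expected loss. A steep rise still does not make the null right; the test then shows dose-dependence.

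Three further inferences go beyond the document:
- That the model adjusts for SHA and PPT values altered by naloxone. Both are measured at baseline and during infusion (sections 9.1.1 and 9.2.6), and 13.2.1 does not say which values enter.
- That deleting factors at P > 0.05 contradicts α = 0.01. A retention threshold need not equal the test level.
- That a mere difference between steps would be declared a success. Section 13.2.1 has no success rule, and the interim rule refers to the drug difference.

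Finally, rank sum may be a slip for signed rank, since it stands beside a paired t-test. The wording still names the unpaired test.

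**Conclusion.** The concern holds in this form: the test assigned to the TME primary outcome does not match the stated null hypothesis, the highest-step definition of the outcome or the sample size, and the drug term in the mixed model is not estimable. The first and last of these follow from the definition of ΔSPID and need no assumption.

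The loss of power cannot be given as one number. It depends on the dose-response shape and the between-step correlation, neither of which the protocol gives. It runs from almost total, when the effect is equal at all steps, to none when the effect appears mainly at step 3. The calculations also take over the plan's own SD, which is that of summed baseline pain, as the SD of ΔSPID. The rank sum figures rest on assumed within-subject correlations; at zero correlation that test loses nothing.

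This should be corrected before any data are analysed, because it concerns the primary test and the interim decision.

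**What to change.** In section 13.2.1, replace the ANOVA sentence by one primary test: H0 mean ΔSPID = 0 at the highest TCI-step reached in both sessions (the same step for naloxone and placebo), two-sided α = 0.01, paired t-test or, if normality fails, Wilcoxon signed-rank. State in section 13.1.1 that the interim rule uses this test. The matching of steps has to be written down because section 4.2.1.1 allows an infusion to be stopped early. Keep the step ANOVA as a secondary analysis of dose-dependence.

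For the supportive model, take SPID per subject, session and step as outcome, with drug, period, step and drug-by-step as fixed effects and subject as random. Keep and report the drug contrast whatever its P-value. If SHA and PPT are included, use only their baseline values.

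The cost is wording in sections 13.1.1 and 13.2.1. No new data or subjects are needed, and the existing sample size already belongs to the proposed test.

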| 1     | 4     | 4     | 1.1        | 1.1        | 2.2        | 17.8   | 4.22    | 0.55        | 0.55        | 0.55        |
| 1     | 4     | 4     | 1.2        | 1.2        | 2.4        | 18.6   | 4.31    | 0.6         | 0.6         | 0.6         |
| 1     | 4     | 4     | 1.3        | 1.3        | 2.6        | 19.4   | 4.40    | 0.65        | 0.65        | 0.65        |
| 1     | 4     | 4     | 1.4        | 1.4        | 2.8        | 20.2   | 4.49    | 0.7         | 0.7         | 0.7         |
| 1     | 4     | 4     | 1.5        | 1.5        | 3          | 21     | 4.58    | 0.75        | 0.75        | 0.75        |
| 1     | 4     | 4     | 1.6        | 1.6        | 3.2        | 21.8   | 4.67    | 0.8         | 0.8         | 0.8         |
| 1     | 4     | 4     | 1.7        | 1.7        | 3.4        | 22.6   | 4.75    | 0.85        | 0.85        | 0.85        |
| 1     | 4     | 4     | 1.8        | 1.8        | 3.6        | 23.4   | 4.84    | 0.9         | 0.9         | 0.9         |
| 1     | 4     | 4     | 1.9        | 1.9        | 3.8        | 24.2   | 4.92    | 0.95        | 0.95        | 0.95        |
| 1     | 4     | 4     | 2          | 2          | 4          | 25     | 5.00    | 1           | 1           | 1           |

**Table 2.** The variance (V) of the summed pain intensity (SPI) is:

$$V_{SPI} = V_{RP} + V_{MP} + V_{PM} + 2*(COV(RP,MP) + COV(RP,PM) + COV(PM,MP))$$

However, the covariances are unknown, but the table illustrates the relationship between  $V_{SPI}$  (blue column;  $SD_{SPI}$  green column) vis-à-vis different correlations between the variables (RP, MP, PM). A correlation estimate between the variables of 0.5 was used.

E G\*Power version 3.9.1.2, University of Kiel, Germany

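### The non-parametric alternative to the paired t-test in the TME crossover is named as the Wilcoxon rank sum test, an unpaired test; it should be the signed-rank test

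*Protocol*

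**What the plan says.** Protocol section 13.1.1, in its list of sample size assumptions, states that "the design is a placebo-controlled, randomized, double-blind, crossover study". Each participant therefore has a SPID under naloxone and a SPID under placebo, and the primary quantity is the difference between them. The significance level "is set to 0.01 and the power is set to" 0.90. The resulting number is 14, at an effect size of 1.2, with a range of 9 to 19 for effect sizes of 1.7 to 1.0.

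Section 13.2.1 (TME-participants) first tests for normality, then tries a log and after that a Box-Cox transformation if normality fails. It gives a repeated-measures ANOVA or Friedman test for the primary outcome across infusion steps. For comparisons between groups it then names the paired t-test, with this alternative: "Wilcoxon rank sum test will be used, as appropriate for inter-group comparisons". The groups are naloxone and placebo, in the same participants. The section also describes a mixed model with a random subject effect. The signed-rank test is named nowhere in the protocol.

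**The concern.** The two tests offered in one sentence are not counterparts. The paired t-test works on within-subject differences. The rank sum (Mann-Whitney) test compares two independent samples and ignores which naloxone value belongs to which placebo value. Its null distribution is derived under independence, so with correlated pairs its true error rate is not the nominal 0.01 and its power is not that of the paired design. The non-parametric counterpart of the paired t-test is the signed-rank test.

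At stake is the direct naloxone-versus-placebo comparison, should the data stay non-normal after transformation. An analyst who follows the text literally would give up the pairing for which the study was sized.

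**Working it through.** **Inputs.** From section 13.1.1: difference of 5 NRS-units (totals 16 and 11), alpha 0.01, power 0.90, and SD of the summed score 4.1. Table 2 gives 4.12 = sqrt(17) for this SD. The plan uses it as the SD of the paired difference, and it is taken as given here. On Table 2 the protocol says "A correlation estimate between the variables of 0.5 was used". That correlation is among the three pain components. It is not the correlation between naloxone and placebo days, which appears nowhere. Sidedness is not stated.

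**1. Reproduce the stated sample size.** Paired t-test, two-sided alpha 0.01, noncentral t with n - 1 degrees of freedom and noncentrality (5/SD) x sqrt(n):

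- SD 4.12: 5/4.12 = 1.21; power 0.880 at n = 13 and 0.913 at n = 14, so n = 14.
- SD 3.0: 5/3.0 = 1.67; n = 9 (power 0.910).
- SD 5.0: 5/5.0 = 1.00; n = 19 (power 0.915).

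All three stated figures match. One-sided calculations give 12, 8 and 16, which do not. As a contrast, an unpaired t comparison with SD 4.1 per condition needs 22 per group and has power 0.67 with 14 per group. The plan's number is therefore a paired, two-sided one.

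**2. Evaluate the fallback as written.** Naloxone and placebo SPIDs are simulated as bivariate normal with between-day correlation rho. The SD of the difference is held at 4.12, so the per-day SD is 4.12/sqrt(2(1 - rho)). For example, at rho 0.5 it is 4.12/sqrt(1) = 4.12, and at rho 0 it is 4.12/sqrt(2) = 2.92. The shift is 5 for power and 0 for type I error; n = 14; exact two-sided critical values at 0.01. Rho is an assumption, shown as a range.

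| rho | rank sum power | rank sum type I error |
|---|---|---|
| -0.3 | 0.97 | about 0.02 |
| 0 | 0.93 to 0.94 | 0.009 |
| 0.25 | 0.86 to 0.87 | 0.004 |
| 0.5 | 0.67 | below 0.001 |
| 0.75 | 0.23 | below 0.0001 |

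Where a range is given, repeat simulation runs differ in the second decimal.

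**3. Evaluate the paired tests on the same data.** Both depend only on the differences, whose SD is fixed, so rho does not matter. Power is about 0.91 for the paired t-test, with type I error 0.010. For the signed-rank test, power is about 0.89 and type I error just under 0.01. At n = 15 signed-rank power is about 0.92, and at n = 18, the number the plan sets to allow for drop-outs, about 0.98.

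**The case against.** The best reply is that this is a slip of naming. The test beside it is paired, the preceding sentence uses within-subject methods, and the outcome is defined as a single within-subject difference, to which a two-sample test cannot be applied directly. That is plausible, but nothing in the protocol corrects the name, and a literal reader would compare the two sets of SPIDs.

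Three further objections stand and limit the point:

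- **Power and sample size.** A reader might infer that the planned 90% power and 1% error rate do not belong to the trial's test. They belong to the paired t-test, which is named first and is right. The repeated-measures analysis and the mixed model are also specified, so the rank sum test is not the only analysis of the primary outcome.
- **Likelihood of use.** A reader might infer from the 0-10 ratings and low resting pain that the fallback will probably be needed. The documents do not show this. Two transformations come first, and the quantity tested is a difference of changes in a three-item sum. In a simulation with integer ratings at the plan's component means and SDs, and an additive drug effect, a Kolmogorov-Smirnov test with Lilliefors correction rejected normality in 6 to 8% of runs, and the uncorrected test in under 0.1%. Against this, neither a log nor a standard Box-Cox transformation accepts the zero or negative values that a change score can take, so the fallback remains reachable.
- **Size of the loss.** A reader might quote a loss of 22 to 24 points of power (0.67 at rho 0.5, against 0.89 for signed-rank or roughly 0.90 planned). That rests on an assumed rho of 0.5. SPID is already a change from same-day baseline, so a stable subject pain level cancels. The same simulation gave between-day correlations of only 0.00 to 0.03. A material rho would need a shared response to infusion as well. The power figures also come from normal data, for which the plan would use the t-test.

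On the interim look, section 13.1.1 says: "If the null hypothesis (no statistical difference between the placebo and the naloxone groups) is rejected, the study is deemed completed". It names no test for that look, so it does not establish that the rank sum test would drive the decision.

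**Conclusion.** The point holds as a wrong test named for a conditional fallback. The paired t-test and the sample size of 14 are sound on this point and reproduce exactly. If the fallback is used as written, the consequence runs from almost none at rho near 0 (power about 0.93 to 0.94, error about 0.009) to severe at high positive correlation (power 0.23 at rho 0.75). For rho of 0 or more the test does not exceed its 1% error rate; at rho -0.3 it does, at about 0.02. It is therefore neither uniformly conservative nor a general source of false positives.

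These figures assume bivariate normal SPIDs, an SD of the difference of 4.12, and a correlation that the protocol leaves unstated. They show how the test behaves and do not forecast a particular loss. The protocol alone was available. Because it names a specific test, this is a statement to correct and not a detail left open for a statistical analysis plan.

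**What to change.** In section 13.2.1 (TME-participants), replace the rank sum test with the Wilcoxon signed-rank test on the within-subject difference SPID_NX - SPID_PL. State that the same paired test applies if the interim comparison at 14 participants is done non-parametrically. Make the change before any unblinded analysis, so that the choice of test cannot appear driven by the data.

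The cost is a few words. No change to data collection, procedures or participant numbers is needed: signed-rank power is about 0.89 at 14 participants and about 0.98 at 18 under the plan's own inputs.
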